#### On-road driving assessment (RDA)

1.3.2

Complementary to the neuropsychological assessment, the RDA is considered as the “gold standard” in multiprofessional evaluation. The ecological nature of the on-road situation provides an opportunity to assess patients’ actual driving ability, enabling the adoption of compensatory strategies in the event of cognitive sequelae.

According to Michon’s hierarchical model, driving activity calls for three levels of skills and control, whose involvement varies according to the driver’s mental workload and the time constraints of the situation (Michon, 1985). The operational level involves a high time constraint (in the order of milliseconds) and a low cognitive workload, as it involves automatic action patterns. This level provides vehicle control, requiring quick and undemanding actions from the driver, such as manipulating the car controls or positioning the vehicle in the traffic lane. The intermediate tactical level involves a slightly lower time constraint during driving (in seconds) but calls on slightly higher-level cognitive processing systems, enabling the vehicle to be maneuvered in its environment. It is involved in situations requiring the driver to implement coping strategies that take into account both the perceived environment and the driver’s own driving goals (e.g., slowing down in heavy traffic or when visibility is poor). Finally, the strategic level involves a very low time constraint (in the order of minutes or even hours) but calls on very high-level cognitive functions, mainly upstream of the driving situation. In particular, it involves advance planning (before driving) and decision-making by the driver according to both external conditions (e.g., weather, traffic conditions) and the driver’s internal dispositions (e.g., fatigue, mood, and self-assurance). For example, the driver may choose to postpone departure to avoid traffic jams.

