#### Statistical analysis

2.3.3

To meet the main and secondary A and B objectives, concordance tests will be used to verify that two independent abilities to resume driving measures (two tests) of the same modality—“Favorable” or “Unfavorable”—are equal. Concordance analyses between tests (binary variables) will be expressed in the form of concordance percentages, simple kappa coefficient and its 95% confidence interval. Analyses between TRIP (continuous variable) and other tests (binary variables) will be conducted using *t*-tests or Mann–Whitney tests depending on the TRIP score distribution. Multivariate regression will also be used to study measures’ concordance and prediction levels, for both objectives. It will be logistic or linear, depending on the studied variable (i.e., approved doctor’s opinion for objective A and TRIP results for objective B).

A sensitivity and specificity analysis of the approved doctor’s opinion will also be carried out. Performance metrics (Secondary Objective C) will be calculated from the confusion matrix values (Table 4):$$\mathrm{Accuracy:}\frac{RP+RN}{RP+RN+FP+FN}$$$$\mathrm{Sensitivity (Se):}\frac{RP}{RP+FN\text{.}}$$$$\mathrm{Specificity (Sp):}\frac{RN}{FP+RN}$$$$\mathrm{Positive predictive value (PPV) or Precision (Pr):}\frac{RP}{RP+FP}$$$$\mathrm{Negative predictive value (NPV):}\frac{RN}{FN+RN}$$

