#### Relevance of the neuropsychological assessment

3.1.1

- In the event of concordance between the neuropsychologist’s opinion and other assessments (RDA, multiprofessional, approved doctor’s opinion), the neuropsychological assessment can then be considered to be a good predictor of driving ability, particularly by shedding light on the driving restrictions to be recommended.- In the event of a discrepancy between the neuropsychologist’s opinion and other assessments (RDA, multiprofessional, approved doctor’s opinion), the neuropsychological assessment cannot be considered a reliable predictor of driving ability, in line with the mixed findings reported in the literature (Wolfe and Lehockey, 2016; McKay et al., 2016; Ortoleva et al., 2012). However, this assessment will still be of obvious interest for detecting any reduction in useful field of view, raising awareness of certain deficits, or suggesting rehabilitation options adapted to the person’s cognitive profile. The neuropsychologist’s role is decisive in the project to resume driving (Perna et al., 2021).- Neuropsychological tests whose scores are significantly correlated with the TRIP score can be considered the most predictive of driving ability. These results will help guide the choice of neuropsychological tools.

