#### Relevance of on-road assessment

3.1.2

- In the event of concordance between opinion following RDA and other assessments (neuropsychological, multiprofessional, approved doctor’s opinion), the assessment tools mentioned can be considered to be good predictors of driving ability, in accordance with the literature (Marshall et al., 2007).- In the event of a discrepancy between RDA and other assessments, the RDA value will remain undeniable, but results can be explored and discussed depending on which assessment there is a discrepancy with, and the direction of this discrepancy. More specifically, a discrepancy between RDA and neuropsychological assessment can highlight coping strategies linked to awareness of cognitive disorders. In fact, correlation between neuropsychological assessment and actual driving may depend on the individual’s level of awareness of their abilities (Griffen et al., 2011). These results would not, therefore, call into question value of the RDA. On the other hand, a discrepancy between the opinion given following RDA and that given by the PRM doctor (multiprofessional evaluation) or the approved doctor may raise questions about value of the RDA, or at least the importance attached to it by doctors (PRM or approved doctor).- In the event of concordance between the TRIP score and the various assessments, TRIP can be considered a relevant tool for predicting driving ability. Conversely, in the event of discrepancies between TRIP and other assessments, the usefulness of this grid can be discussed. Further analysis could highlight the relevance of certain sub-scores.- In the event of concordance between the number of interventions on the controls and professional opinions, this criterion can then be considered to be a good predictor of driving ability. On the other hand, in the event of discrepancies, a certain tolerance may be accepted if the driving instructor intervenes on the controls during RDA.

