#### Relevance of multiprofessional evaluation

3.1.3

- Agreement between the multiprofessional opinion and that of the approved doctor will enable the approved doctor to get additional information, in line with this evaluation recommended by the HAS and now mandatory.- A discrepancy between the multiprofessional opinion and that of the approved doctor will help to identify situations for which an opinion is difficult to formulate. Using the scientific evidence gathered, an analysis of advantages and disadvantages can be carried out to shed more light on the fitness to drive evaluation, with a view to helping approved doctors identify the best tools for deliberating their opinions.

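### Section 3.1.1 uses the approved doctor's opinion as a yardstick for whether the neuropsychological assessment predicts driving ability, but that comparison measures how far doctors follow the assessment

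*Protocol article*

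**What the plan says.** The Discussion of the protocol article sets out in advance how the concordance results will be read.

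- **Section 3.1.1, neuropsychological assessment.** If it is concordant with the listed comparators (the RDA, the multiprofessional opinion and the approved doctor's opinion), it counts as a good predictor of driving ability. The discrepancy bullet has the same list and concludes that "the neuropsychological assessment cannot be considered a reliable predictor of driving ability, in line with the mixed findings reported in the literature". The bullet adds that the assessment keeps other uses, but does not ask which side of the disagreement is at fault.
- **Section 3.1.2, RDA.** The first bullet also counts agreement with the approved doctor towards being a good predictor. On disagreement the text is protective: "In the event of a discrepancy between RDA and other assessments, the RDA value will remain undeniable". Where the disagreement is with a doctor, it "may raise questions about value of the RDA, or at least the importance attached to it by doctors (PRM or approved doctor").
- **Section 3.1.3, multiprofessional evaluation.** Disagreement with the approved doctor "will help to identify situations for which an opinion is difficult to formulate". It is not held against the evaluation.

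Three other places bear on the doctor's role:

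- Section 1.2 says that approved doctors often differ in interpreting the multiprofessional evaluation, probably because of gaps in condition-specific training and uneven expertise. It gives no rate.
- Section 1.3.2 says that "the RDA is considered as the “gold standard” in multiprofessional evaluation".
- Section 2.2.1.6 says that participants receive the multiprofessional report among the papers for the doctor's visit.

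Under section 2.3.3, agreement between binary opinions is "expressed in the form of concordance percentages, simple kappa coefficient and its 95% confidence interval". The article gives no cut-off that separates concordance from discrepancy.

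**The concern.** A comparator can show that an assessment predicts driving ability only if it is a reasonable stand-in for driving ability. By the article's own account the approved doctor's opinion is not one. It varies between doctors, and it is formed with the multiprofessional report available. It is also something the study hopes to improve, since section 3.4.2 foresees using the results in training approved doctors.

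The error can run in either direction. If doctors vary for reasons unrelated to the patient, that variation lowers agreement and section 3.1.1 charges it to the neuropsychological assessment. If doctors simply follow the report, agreement is high whether or not the assessment is right, and section 3.1.1 credits it with prediction.

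Section 3.4.2 notes that the decree omits neuropsychological assessment, and the study hopes to inform that debate. A finding that the assessment is unreliable, produced by inconsistency among doctors, would work against that aim.

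**Working it through.** **1. The reading rules side by side.** The article states no agreement figure to reproduce, so the main check is of the text.

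| Opinion compared with the approved doctor | Reading of disagreement | Doctors offered as an explanation? |
|---|---|---|
| Neuropsychological (3.1.1) | Not a reliable predictor, though other uses remain | No |
| RDA (3.1.2) | Value retained; may be questioned | Yes, the weight doctors give it |
| Multiprofessional (3.1.3) | Marks cases that are hard to judge | Not named; the difficulty lies with the case |

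One kind of disagreement is thus read in three ways, and only the first puts the failure on the assessment without an alternative.

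**2. Can variation among doctors alone produce disagreement?** The document gives neither input, so both are assumptions:

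- p = 0.60, the share truly fit;
- e = 0.10 to 0.25, the share of cases in which the doctor departs from the truth at random.

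The assessment is taken to be always right. In the layout of Table 2:

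- a = p(1−e), both favorable;
- b = (1−p)e, assessment unfavorable and doctor says fit;
- c = pe, assessment favorable and doctor says unfit;
- d = (1−p)(1−e), both unfavorable.

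Observed agreement is Po = a + d = 1 − e. The doctor's fit share is f = p(1−e) + (1−p)e. Chance agreement is Pe = pf + (1−p)(1−f). Kappa = (Po − Pe)/(1 − Pe).

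| e | Po | f | Pe | Kappa |
|---|---|---|---|---|
| 0.10 | 0.90 | 0.58 | 0.348 + 0.168 = 0.516 | 0.384/0.484 = 0.79 |
| 0.15 | 0.85 | 0.57 | 0.342 + 0.172 = 0.514 | 0.336/0.486 = 0.69 |
| 0.20 | 0.80 | 0.56 | 0.336 + 0.176 = 0.512 | 0.288/0.488 = 0.59 |
| 0.25 | 0.75 | 0.55 | 0.330 + 0.180 = 0.510 | 0.240/0.490 = 0.49 |

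**3. Sensitivity to the assumed share fit.** With p = 0.50, kappa is 0.80, 0.60 and 0.40 at e = 0.10, 0.20 and 0.30. In 4,000 simulated samples of the planned 100 participants, the 95% sampling ranges are 0.67 to 0.92, 0.43 to 0.75 and 0.21 to 0.57. With p = 0.30 or 0.70, kappa is 0.77, 0.56 and 0.36. The pattern does not depend on the choice of 60%.

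**4. The opposite case.** If the report followed the neuropsychologist's opinion and the doctor followed the report every time, then b = c = 0 and, provided both categories occur, kappa = 1 whatever the accuracy of that opinion.

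**The case against.** The strongest reply is that these are discussion statements in an exploratory study, and that the operative sections already keep the issues apart. The main criterion (2.3.1.1) leaves the approved doctor out. Agreement with the doctor is a separate secondary criterion (2.3.1.2). The doctor's opinion is itself assessed for sensitivity and specificity (2.3.3) and is one of the predictors set against perceived road risk (2.3.2.1). The neuropsychological tests called most predictive are chosen by correlation with the TRIP grid. All of this is correct. It confines the point to how results are read; no test or table is wrong. It does not remove the point, because section 3.1 is where the article says what the concordance results will mean.

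A reader might infer three stronger claims that the document does not support.

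- **That the RDA could also be declared unreliable.** Section 3.1.2 says only that disagreement with the rehabilitation physician "or the approved doctor may raise questions about value of the RDA". The sentence goes on to offer the importance doctors attach to it as the alternative, and the bullet opens by keeping its value intact.
- **That disagreement with the doctor alone condemns the neuropsychological assessment.** Section 3.1.1 lists three comparators together and does not say whether one suffices. The ambiguity is a reason to reword, but it does not show that the doctor overrides the other two.
- **That a kappa of a given size would trigger the verdict.** No cut-off is stated, so the calculation shows a mechanism and does not forecast a downgrade.

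It is also fair to say that section 1.2 speaks of interpreting the multiprofessional evaluation, not the neuropsychologist's opinion taken alone, and that departures by doctors who hold the report need not be random.

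**Conclusion.** The point stands for section 3.1.1, and for the single bullet in 3.1.2 that counts agreement with the approved doctor as evidence of good prediction. On the article's own description, agreement with the doctor measures how far doctors follow an assessment. It cannot show whether the assessment predicts driving ability. Followed as written, the 3.1.1 rule can lead to a wrong conclusion about the neuropsychological assessment, and it conflicts with the readings in 3.1.2 and 3.1.3.

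The size is illustrative: kappa falls to 0.79 at 10% and 0.49 at 25% random departure, with a faultless assessment and 60% fit. Those rates, the 60% and the randomness are assumptions. The inconsistency between the three sections depends on none of them.

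**What to change.** 1. In 3.1.1, remove the approved doctor's opinion from the list of comparators in both the concordance and the discrepancy bullets. The RDA and the multiprofessional opinion stay.
2. In 3.1.2, remove it from the first bullet, which names good predictors. Keep the discrepancy text as it is, including the clause on the importance doctors attach to the RDA.
3. Report objective A for each assessment (neuropsychological, RDA, multiprofessional) as agreement with, or uptake by, the approved doctor. Show direction: how often a favorable opinion is followed by unfit, and an unfavorable one by fit.
4. Add a sentence to 3.1.1 saying that disagreement with the approved doctor will be read as it is in 3.1.2 and 3.1.3, as a sign of the weight doctors give the assessment or of cases that are hard to judge. Without it, the neuropsychological comparison with the doctor would have no stated reading, because 3.1.3 covers only the multiprofessional opinion.

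The cost is a few sentences. Data collection, Table 2 and the kappa analysis do not change; the directional percentages come from the same four cells.

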##### Neuropsychological assessment

2.2.1.2

This assessment is carried out by a psychologist specialized in neuropsychology. It includes a series of validated standardized tests investigating attentional, executive and psycho-behavioral functions. The list of tests was co-constructed according to different criteria:- psychometric qualities (sensitivity, validity, reliability)- relevance established in the literature in relation to driving ability evaluation- availability and frequency of use in current practice (assessed through a survey of rehabilitation centers)- administration conditions (essentially non-verbal tests for use with patients with expressive aphasia; non-bimanual tests allowing inclusion of patients with hemicorporeal deficits; duration deemed acceptable and equipment easy to obtain and use).

The neuropsychological assessment lasts around 3 h, divided into two one-and-a-half-hour sessions, each with a five- to ten-minute break. The order of administration of the tests was established so as to alternate tasks according to their format (computerized vs. paper-and-pencil), their mental load (higher or lower), their sensitivity to fatigue, and the cognitive functions called upon. The standardized neuropsychological assessment protocol is described in the case report form. It includes the following tests: Alertness (TAP 2.3.1), Divided attention (TAP 2.3.1), Epworth scale, Trail-Making-Test (TMT), Go/Nogo (TAP 2.3.1), Basic Empathy Scale in Adults (BES-A), Neglect with central task (TAP 2.3.1), Tour of London (TOLDX 2^nd^ edition), Working memory difficulty level 3 (TAP 2.3.1), Sustained attention color-or-form version (TAP 2.3.1) and UPPS Impulsive Behavior Scale. Lastly, the Brain Injury Driving Self-Awareness Measure—BIDSAM (Gooden et al., 2017) is part of the neuropsychological assessment, but will be completed following the RDA.

For each test, the examiner collects raw and standardized scores (each participant’s performance is compared to the standard group). Based on this assessment, the neuropsychologist then issues an opinion (favorable, unfavorable or reserved) on the estimated compatibility between the participant’s cognitive functions and the return to driving.

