##### On-road driving assessment (RDA)

2.2.1.4

A driving instructor and a therapist carry out this 45-min assessment in a dual-control driving school car. In order to limit variability linked to the geographical diversity of the rehabilitation centers, driving routes were standardized between centers to ensure that they were comparable in terms of the traffic and road situations encountered. This route standardization was established in accordance with recommendations certified by the HAS (Haute Autorité de Santé, 2016). The TRIP (Test Ride for Investigation Practical fitness to drive) observation grid and scoring system are detailed in the case report form. Quantified measures of driving performance are collected during the assessment (15 sub-scores and a total score out of 100). The professionals present in the vehicle fill in this grid jointly after the RDA. The main interest of this grid, and the reason for its choice in this study, lies in the relevance of the tactical and strategic compensation scores in relation to Michon’s (1985) model. These scores reflect the behavioral self-regulation mechanisms adopted by drivers in order to compensate for any cognitive disorders and guarantee homeostasis of the task difficulty as described in the TCI model. Following this assessment, professionals issue an opinion on the participant’s driving ability (favorable, unfavorable or reserved).

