### Analysis

2.3

Participant characteristics and assets will be described and compared. Reasons for refusing to participate will be collected. Descriptive statistics on participant characteristics will be presented. The characteristics of participants included will be compared with those of non-included participants in the eligibility register to ensure their representativeness. Quantitative variables will be described in terms of mean, standard deviation, median, interquartile range and extreme values. Qualitative variables will be described in terms of absolute frequency and percentage per modality. The alpha threshold for statistical significance is set at 5%; 95% confidence intervals will be presented. All the variables collected for people included in the study will be described. Missing data will not be replaced in this study and some participants might be secondary excluded from certain analyses. Sub-group analyses may be carried out, if statistically robust, depending on the number of fitted cars required and the conclusion of the medical examination.

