###### Secondary criterion B: concordance professional assessment / TRIP grid

2.3.1.2.2

An analysis identical to the main objective will be carried out, cross-referencing the results of the professional assessments with that of the TRIP, expressed as a binary variable Favorable / Unfavorable (Table 3).

**Table 3 tab3:** Evaluation criteria of the secondary objective B for contingency table.

		Assessment x_i_	
		Favorable	Unfavorable
TRIP grid	Favorable	*a*	*b*
	Unfavorable	*c*	*d*

The TRIP score will also be analyzed continuously (total adjusted score out of 100), in total and by sub-score. Correlation analysis will also be carried out between the raw results from the neuropsychological tests and the TRIP grid, in order to identify the neuropsychological tools most predictive of driving ability in real-life situations.

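### Calling tests most predictive because they correlate significantly with TRIP does not rank them: at n = 100 a correlation of about 0.20 earns the same label as a strong one

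*Protocol article*

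**What the plan says.** All references are to the protocol article.

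- **Planned analysis.** Section 2.3.1.2.2 (secondary criterion B): "Correlation analysis will also be carried out between the raw results from the neuropsychological tests and the TRIP grid". The stated purpose is to find the neuropsychological tools that best predict real-life driving ability. The same section says that TRIP is analysed as a continuous score, both overall and for each sub-score.
- **Reading rule.** Section 3.1.1: "Neuropsychological tests whose scores are significantly correlated with the TRIP score can be considered the most predictive of driving ability". Its use follows directly: "These results will help guide the choice of neuropsychological tools".
- **Threshold.** Section 2.3: "The alpha threshold for statistical significance is set at 5%; 95% confidence intervals will be presented". No adjustment for multiple tests appears in the article.
- **Instruments.** Section 2.2.1.2 lists eleven: alertness, divided attention, Epworth, TMT, Go/Nogo, BES-A, neglect, Tower of London, working memory, sustained attention and UPPS. The BIDSAM is the twelfth; it "is part of the neuropsychological assessment, but will be completed following the RDA".
- **TRIP scores.** Section 2.2.1.4: "15 sub-scores and a total score out of 100".
- **Related analyses.** Section 2.3.3 plans multivariate regression for objective B, with TRIP results as the variable studied.
- **Status.** Sections 2.1 and 2.4 call the study exploratory. The target in section 2.1 is 100 participants.

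**The concern.** Whether a test is the most predictive is a comparative question, and its answer needs the size of each association and the precision of that size. The section 3.1.1 rule answers a different, yes/no question: is the correlation distinguishable from zero? Every test that passes gets the same label, however weak or strong its association.

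A second issue makes this worse. The same yes/no rule is applied to a battery of instruments at a flat 5%, so some tests may earn the label by chance.

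The consequence is practical. The outcome is meant to inform which tests rehabilitation centers use. Section 3 expects the study to underpin recommendations that now rest on expert agreement, and section 3.4.2 restates the hope of identifying the best-performing tools. A list that mixes strong, trivial and chance associations would not serve that purpose.

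**Working it through.** The article gives no figure for these correlations. Its only design calculation (section 2.1) concerns a t-test, so there is nothing to reproduce here.

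**Inputs.** n = 100 (section 2.1); alpha = 0.05 (section 2.3); 12 instruments (section 2.2.1.2); 1 TRIP total and 15 sub-scores (section 2.2.1.4). Assumptions: a two-sided test of a Pearson correlation, one score per instrument, and complete data.

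**Step 1. The smallest correlation that earns the label.**
r_crit = t / √(n − 2 + t²), with t(0.975; 98) = 1.984.
r_crit = 1.984 / √(98 + 3.94) = 0.197, and r² = 0.039, so under 4% of variance.
- If exclusions for missing data left n = 80 (an assumption), r_crit would be 0.220 and r² 4.8%.
- One-sided, with t = 1.661, r_crit would be 1.661 / √(98 + 2.76) = 0.165, so the bar would be lower.

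**Step 2. What the rule treats as equal.** Fisher-z interval: tanh(atanh(r) ± 1.96/√97).

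| Observed r | 95% CI | Variance explained | Label |
|---|---|---|---|
| 0.20 | 0.00 to 0.38 | 4% | most predictive |
| 0.50 | 0.34 to 0.63 | 25% | most predictive |

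For a true r of 0.20, power is about Φ(atanh(0.20) × √97 − 1.96) = Φ(2.00 − 1.96), or about 51%. Whether such a test gets the label is close to a coin toss.

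**Step 3. Chance labels, 12 instruments against the TRIP total.** Suppose that no instrument is related to TRIP.
- Expected false labels: 12 × 0.05 = 0.6.
- At least one, if independent: 1 − 0.95¹² = 0.46. With 11 instruments (BIDSAM left out): 1 − 0.95¹¹ = 0.43.
- Instruments in one battery are correlated. In a simulation under the null (4,000 runs, n = 100, equal correlations between instruments), the chance of at least one false label was about 39-40% at an assumed correlation of 0.3 and about 32% at 0.5.

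**Step 4. Only if the sub-scores are tested too.**
- Pairs: 12 × 16 = 192. Expected false positives under the same null: 192 × 0.05 = 9.6.
- In the simulation, with assumed correlations of 0.3-0.5 between instruments and 0.3-0.7 between sub-scores, about 3 to 6 of the 12 instruments were significant on at least one TRIP score by chance.

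**Step 5. The price of error control, with Bonferroni as a simple illustration.** For 12 tests, alpha = 0.05/12 = 0.0042. The critical |r| rises from 0.197 to 0.284, and the correlation detectable with 80% power rises from 0.28 to 0.36.

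**The case against.** There is a fair case for leaving this alone.

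- **The missing correction may not be missing.** The article is silent on multiplicity; it does not say that the correlations will go unadjusted. A separate analysis plan may deal with it. This stands, so the absence of a correction is not a fault in itself. It does not touch the main point, because an adjusted p-value ranks tests no better than an unadjusted one.
- **The family may be 12, not 192.** A reader might infer that 192 correlations and 9.6 false positives are what the plan commits to, or even a minimum. The text does not support that. Section 3.1.1 speaks of the TRIP score in the singular, section 2.3.1.2.2 does not say that sub-scores enter the correlations with the neuropsychological tests, and section 3.1.2 presents sub-scores as possible further analysis. The larger figures are conditional. Nor does the article say how many raw scores each test yields, so no count should be built on that.
- **Some tests are probably related to driving.** The introduction cites evidence for attention, executive function and working memory. The chance figures describe the case of no association and are not a forecast. But if many tests are truly related, significance separates strong from weak even less well.
- **Better outputs are already planned.** Confidence intervals (section 2.3) and regression (section 2.3.3) would both help. This stands and makes the fix easy, but the section 3.1.1 rule uses neither.
- **The study is exploratory and the sentence sits in the Discussion, in permissive wording.** True, and the correlations belong to a secondary criterion. That limits how serious the point is. It does not remove it, because the results are meant to inform the choice of tools.

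**Conclusion.** The point holds as a fault in a stated rule. Using significance at 5% as the mark of the most predictive tests cannot meet the aim in section 2.3.1.2.2, because at n = 100 any |r| of about 0.197 or more, under 4% of variance, qualifies equally with a much stronger correlation. This rests only on the stated threshold, the target sample size and a two-sided test.

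The multiplicity part is secondary and conditional. With the TRIP total as the only target and no true association, the chance of at least one false label is 46% under independence, or roughly 32-40% under assumed correlations of 0.3-0.5 between instruments. It also assumes that no adjustment is specified elsewhere. The 192 pairs and 9.6 expected false positives apply only if all sub-scores are tested.

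The main criterion, agreement between professional opinions, is unaffected. What changes is what the study can say about which neuropsychological tests to prefer.

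**What to change.** 1. Rewrite the section 3.1.1 rule so that tests are ranked by the size of their correlation with the TRIP total, each with its 95% confidence interval. Tests whose intervals overlap widely should not be presented as clearly ordered.
2. Name one main score per instrument, and name the TRIP total as the target, before the data are analysed.
3. Read the ranking alongside the regression already planned in section 2.3.3, which shows what the tests contribute jointly.
4. Apply Holm or false-discovery-rate control across the 12 instruments to any statement of significance. If the analysis plan already does this, say so in one sentence.
5. Treat correlations with the 15 sub-scores as descriptive.

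The cost is wording and modest programming, with no new data and no added burden on participants. The downside is that fewer tests will be declared significant: under the Bonferroni illustration, the correlation detectable with 80% power rises from 0.28 to 0.36. Penalized regression, cross-validation or bootstrapped ranks could be added but are optional.
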